# StOP? II trial: cluster randomized clinical trial to test the implementation of a toolbox for structured communication in the operating room—study protocol

**DOI:** 10.1186/s13063-022-06775-y

**Published:** 2022-10-18

**Keywords:** Operating room, Teamwork, Communication, Coordination, Briefing, Checklist, Post-operative complications, Mortality, Cluster randomized controlled trial

## Abstract

**Background:**

Surgical care, which is performed by intensely interacting multidisciplinary teams of surgeons, anesthetists, and nurses, remains associated with significant morbidity and mortality. Intraoperative communication has been shown to be associated with surgical outcomes, but tools ensuring efficient intraoperative communication are lacking. In a previous study, we developed the StOP?-protocol that fosters structured intraoperative communication. Before the critical phases of the operation, the responsible surgeon initiates and leads one or several StOP?s. During a StOP?, the surgeon informs about the progress of the operation (status), next steps and proximal goals (objectives), and possible problems (problems) and encourages all team members to voice their observations and ask questions (?). In a before-after study performed mainly in visceral surgery, we found effects of the StOP?-protocol on mortality, length of hospital stay, and reoperation. We intend to assess the impact of the StOP?-protocol in a cluster randomized trial, in a wider variety of surgical specialties (i.e., general, visceral, thoracic, vascular surgery, surgical urology, and gynecology). The primary hypothesis is that the consistent use of the StOP?-protocol by the main surgeon reduces patient mortality within 30 days after the operation. The secondary hypothesis is that the consistent use of the StOP?-protocol by the main surgeon reduces unplanned reoperations, length of hospital stay, and unplanned hospital readmissions.

**Methods:**

This study is designed as a multicenter, cluster-randomized parallel-group trial. Board-certified surgeons of participating clinical departments will be randomized 1:1 to the StOP? intervention group or to the standard of care (control) group. The intervention group will undergo a training to use the StOP?-protocol and receive regular feedback on their compliance with the protocol. The surgeons in the control group will communicate as usual during their operations. The unit of observation will be operations performed by cluster surgeons. Consecutive patients will be enrolled over 4 months per cluster. A total of 400 surgeons will be recruited, and we expect to collect patient outcome data for 14,000 surgical procedures.

**Discussion:**

The StOP?-protocol was designed as a tool to structure communication during surgical procedures. Testing its effects on patient outcomes will contribute to implementing evidenced-based interventions to reduce surgical complications.

**Trial registration:**

ClinicalTrials.gov NCT05356962. Registered on May 2, 2022

**Supplementary Information:**

The online version contains supplementary material available at 10.1186/s13063-022-06775-y.

## Background

Each year, about 4.2 million people die within 30 days following a surgical procedure [1]. Further decreasing mortality after surgical procedures therefore warrants continuing effort. Surgical quality has an impact not only on mortality but also on other clinical outcomes such as unplanned reoperations [2].

Outcomes of operations depend on many factors. Patient factors are pivotal; additional factors include structural as well as procedural aspects [3]. Regarding the quality of the surgical procedure proper, surgeon experience and surgeon caseload [4, 5] as well as surgeon technical skills [6, 7] play a major role.

There is mounting evidence, however, that communication and teamwork within the surgical team are important for patient outcomes, and studies are needed that aim at improving teamwork and assessing clinical patient outcomes [8]. Research showed problems in about 30% of communication during operations, causing delays, tensions in the team, inefficiencies and procedural errors [9], undesirable incidents [10], or flow disruptions, that in turn may lead to procedural errors [11]. Regarding *patient outcomes*, our own observational study [12] demonstrated a significantly lower risk of surgical site infections (SSI) when the surgical team communicated about task-related aspects more frequently. In the same study, we observed a higher risk of SSI for teams showing more case-irrelevant communication at the end of the operation, corroborating the results of another study [13] showing a significant relationship between *intraoperative* information sharing and patient outcomes.

Core aspects of effective communication are creating and maintaining high levels of situation awareness in surgical teams—this is a (shared) perception and knowledge regarding important elements and the development of the situation that indicate (or allow to predict) a need for action [14, 15]. Situation awareness requires a shared understanding of the characteristics and requirements of the task in general (often called “shared mental model”) [14]. Another interesting focus is on communication practices that aim at team reflexivity [16, 17], which includes not only an overt reflection in the team, but also reflective communication about the team’s objectives, strategies, and processes [18]. In-action team reflection (reflecting during the process) was related to team performance in simulated medical emergencies [17].

Common methods to improve communication in the OR are based on *checklists* and briefings [19], typically conducted before or after an operation. Checklists help to structure the communication of clinically relevant information and were introduced because missing or faulty information regarding important aspects of the operations (e.g., patient identity, surgical procedure) represented a serious threat to patient safety. However, if checklists are too long, people may develop “checklist fatigue” [20], regard them as trivial or obvious, and may reduce adherence or use it as a “checkbox exercise” [21]. A second approach to improve communication is based on *general teamwork and communication training*, typically conducted in a specific training setting. Although such training settings may be realistic (e.g., high-fidelity simulations) [22], they can only teach general principles (e.g., “you should make sure that your communication has been received properly”) that need to be transferred to other situations. However, transfer of training is not easy to achieve [23], and training effects may not sustain over time [24]. Furthermore, it is often not easy to motivate participants for training. In surgery, this applies notably for experienced surgeons [25]. Success, i.e., reduction in intraoperative problems, morbidity, and mortality, has been reported both for the introduction of checklists [21] and for teamwork training [26–28]. However, findings are not unequivocal for both [8, 21, 28, 29]. Difficulties and obstacles to transferring training to clinical practice are regularly reported in the literature [21, 25, 30]. Careful implementation of interventions into surgical practice thus requires particular attention.

### The StOP?-protocol

In an attempt to encourage structured information exchanges during surgical procedures, we developed an intervention aimed to assure structured information exchange during operations, the StOP?-protocol [31]. The StOP?-protocol is a short intra-operative briefing, initiated by the main surgeon with the aim to inform the entire OR team about the operation. First, the surgeon describes the current *St*atus of the operation (i.e., what has been done, what they are currently doing), then states the *O*bjectives (i.e., the next steps of the operation), the potential *P*roblems they may encounter, and, finally, asks if the team members have contributions or questions (?). The briefing is very short (30–90 s) and requires the attention of the entire OR team (including anesthesia and circulators), who is asked to stop working during the briefing. The StOP?s are used in a flexible way at times when they do not interrupt the flow of the operation or actions that require full attention of the surgeon. The surgeons thus choose when they perform the StOP?-protocol and are asked to announce during the pre-operative team timeout when they intend to perform the StOP?-protocol(s).

In a before-and-after design, the StOP?-protocols were introduced in four surgical departments of four different hospitals (mostly general surgery) in 8256 operations [31] (herein referred to as the StOP? I study). Adjusted intention-to-treat analyses did not show an effect of the StOP?-protocol for surgical site infections (SSI) but did reveal a reduced risk for mortality, unplanned reoperations, and length of stay. The per-protocol analysis supported these findings. Despite promising results, the study has limitations inherent to before-after studies, and sample sizes were calculated based on rates of SSI. To generalize the results, the study needs to be replicated with more hospitals and a more advanced study design. These considerations led us to test the effects of the StOP?-protocol as part of a randomized controlled trial, in a large number of hospitals and various surgical specialties.

## Methods/design

### Objectives

The main objective of the trial is to test if performing the StOP?-protocol improves patient outcomes after operations. The underlying rationale is that by influencing clinical communication within the surgical team during the operation, the StOP?-protocol may improve the quality and safety of surgical care and thereby reduce post-operative mortality and morbidity.

The primary hypothesis is that the consistent use of the StOP?-protocol by the main surgeon reduces patient mortality within 30 days after an operation.

The secondary hypothesis is that the consistent use of the StOP?-protocol by the main surgeon reduces unplanned reoperations and unplanned readmissions up to 30 days after the index operation, and reduces the length of hospital stay.

### Study design

This study is designed as a multicenter, cluster-randomized parallel-group trial. Board-certified surgeons of participating clinical departments form the cluster units will be randomized 1:1 to the StOP? intervention group or to the standard of care group. The unit of observation will be operations performed by cluster surgeons. Consecutive patients will be enrolled over approximately 4 months per cluster (see Fig. 1 for an overview).

**Fig. 1 Fig1:**
[figure not shown]
Study design

We expect that a behavioral intervention targeting the clinical communication of the surgeon will impact the behavior of the entire team present. Surgeons in the intervention group will be trained in the StOP?-protocol with the aim of performing this intervention routinely and consistently during their operations. Because surgeons are specifically trained to adaptively perform the StOP?-protocol, a trial randomizing individual patients or operations is not a feasible study design.

The individual surgeon represents a cluster instead of larger units such as departments or hospitals, for the following reasons: First, the main surgeons have the deepest knowledge of the procedure and its course; furthermore, they bear responsibility for the outcome. Their communication behavior therefore is central to the surgical process [13]. Second, in most hospitals, surgical team stability is rather low. Constant retraining of team members would be necessary if an intervention was dependent on all team members being trained. Taking the individual surgeon as a cluster allows to train the core person to perform the intervention independently of the actual team composition.

### Setting and participants

Study sites will be invited to participate in this trial based on the availability of eligible clusters and operations. The inclusion and exclusion criteria are defined for the cluster level (i.e., the surgeons) and the operation level.

#### Study sites

Study sites, i.e., departments employing surgeons specialized in general, visceral, thoracic, vascular surgery; surgical urology; or gynecology, will be eligible to participate in the study. This choice was guided by the mortality rates of about 1% in these specialties [32–39], which is comparable to general and abdominal surgery included in the StOP? I. Traumatology departments or general surgical departments that include traumatology are included. Cardiac surgery was excluded because of the higher incidence of mortality and already established communicative behaviors typically between the surgeon and the perfusionist. Neurosurgery was excluded because of the minimal number of high-risk procedures performed by a very limited number of surgeons.

#### Surgeons

Board-certified surgeons in one of the specialties of interest will be recruited. Surgeons who are already performing StOP?-protocols (e.g., because they took part in the first StOP? study and surgeons who were previously enrolled in the StOP? II trial (e.g., because they moved or rotated between participating sites) will be excluded. Resident surgeons will not be recruited as clusters, since they either assist or perform surgical procedures under supervision, and since they are still in training, an additional task may interfere with their technical performance.

#### Operations

Elective and emergency operations performed by a cluster (surgeon) during the cluster-specific time period will be considered for inclusion. We expect an operation volume of 30 eligible operations per surgeon within 4 months. This number is the target per cluster but the actual number will vary among surgeons.

Exclusion criteria for operations include the following:Patient age below 18 yearsPrevious operation at the same site up to 30 days prior to the index operationProcedures not done in operating rooms but in outpatient clinics, onwards, etc.Mainly diagnostic endoscopic procedures (e.g., colonoscopy, gastroscopy, bronchoscopy)Percutaneous interventions (e.g., transurethral interventions)Documented refusal of the patient for the use of healthcare-related data

### Recruitment, screening, and informed consent procedure

#### Surgeons

On the participating study sites, board-certificated surgeons will receive detailed information on the study to decide on participating. Each participating surgeon will sign an informed consent defining tasks, responsibilities, potential risks, and benefits. The investigators will explain to each surgeon the nature of the study, its purpose, the procedures involved, and the expected duration. Each surgeon will be informed that the participation in the study is voluntary and that he or she may withdraw from the study at any time.

On the consent form, participants will be asked if they agree to the use of their data should they choose to withdraw from the trial. Participants will also be asked for permission for the research team to share relevant data with people from the universities taking part in the research or from regulatory authorities, where relevant.

#### Patient consent

The StOP?-protocol is an intraoperative briefing addressing communication within the surgical team. The study has no impact on the medical treatment of the patient. Therefore, this study is performed based on a general consent from the patients, where they agree with the use of healthcare-related data that are the result of the patient’s treatment.

### Intervention

The surgeons in the intervention group will undergo a multi-module training on how to use the StOP?-protocol [31]. The training will encompass the following steps: (1) Documentation: the surgeons in the intervention group will receive documentation on the StOP?-protocol, including a leaflet describing the StOPs? and when and how to use them during operations. (2) In-person instructional interview: in a one-to-one instruction, training instructors will conduct a training interview with each surgeon in the intervention group (planned duration: 20 min). Goals of the interviews are to identify the most appropriate moments to initiate StOP?s for the surgical procedures the surgeon performs most often, to discuss details on how to announce and perform the protocol, and to discuss open questions. (3) On-site feedback for at least three operations led by surgeons in the interventional group in the first 2 weeks of the intervention period. An instructor will be present in the OR and observe how the StOP?-protocol is announced and performed. A short, in-person feedback will be given immediately after the operation. (4) During the whole intervention period, adherence to the StOP?-protocol will be assessed at least monthly and results communicated to each surgeon; in the case of adherence issues, the research team will offer support to discuss potential barriers to adherence.

Surgeons in the control group will not be trained. They represent the standard of care, using local practices, and are asked to communicate as usual during their operations. Given the nature of the study, these surgeons will not be blinded to the intervention.

In each participating site, the anesthesiology and OR nurses team will be informed about the study. The information will consist of a presentation of the study by the research team and flyers will be available to inform about the StOP?-protocol and the study goals.

### Measurements

The following data will be collected.

#### Hospital and surgical units

Basic characteristics of the study sites will be recorded, such as the language region, hospital type, number of beds, number of employees, number of operating rooms, yearly operating volume, hospital teaching category, number of staff in training, current practices of the WHO timeout and signouts, and previous team training history.

### Participating surgeons

Data collected about all participating surgeons include age, gender, nationality, native language, year of primary medical degree, year of general and specialized surgery degrees, tenure at the current hospital, tenure in current position; hierarchy level, job title, study arm, and time frame of participation in the study. For surgeons in the intervention group, additional information collected are adherence rates and whether the initial training, and retrainings took place.

#### Patient and operation characteristics

We will collect data about the type of operation, date of admission, date of operation, time of incision, time of last stich, duration, surgical access, level of urgency, and IDs of the surgeons and residents present during the operation. Patient characteristics include gender, age at the time of operation, height, weight, previous laparotomies at the same site 30 days prior the operation, ASA score, and wound contamination class.

#### Intervention adherence

The intervention is a behavioral intervention that requires the surgeon to remember and implement a new behavior pattern; thus, adherence needs to be assessed. Adherence to the StOP?-protocol will be measured for each operation. Adherence is assessed using a standardized reporting form filled in by each scrub technician present during the operation before they leave the operating room. They report if and how many StOP?s were performed during their presence and provide a simple quality rating of the StOP?s on a Likert scale from 1 (very bad) to 5 (very good); a definition of the characteristics of a good StOP? is provided (i.e., spoken loudly enough, complete (StOP? acronym), engaged, the complete team stopped working and paid attention). Adherence of reporting by the scrub technicians will be calculated by comparing the number of operations performed with the number of reports submitted. Adherence to the StOP?-protocol will be calculated by comparing the adherence reports of the scrub technicians for surgeons in the intervention group with the number of operations performed by these surgeons.

#### Endpoints

The primary endpoint is death up to 30 days after the start of the index operation. This information will be provided by the hospital. The hospital obtains the information from patient records and, if not available, via the patients directly, the family, or the general practitioner.

The following secondary endpoints will be assessed:Unplanned reoperation within 30 days is defined as any operation after the end of the index operation for up to 30 days. Only reoperations within the same hospital of the index operation will be considered. The definition of type IIIb (surgical reoperation) of the Clavien-Dindo Classification will be used to define this variable [40]. Data will be obtained from medical records.Length of index hospital stay is defined as days between the index operation to discharge or transfer to another hospital. In-hospital deaths will be recorded and considered as censoring events. Data will be obtained from medical records.Unplanned readmission within 30 days is defined as any unplanned readmission at the same hospital as the index hospital within 30 days after the operation. Readmissions that are mentioned already in the discharge letter of the index hospital stay are considered planned if the reason for the readmission matches to the one described in the discharge letter. Data will be obtained from medical records.We plan to conduct additional analyses on surgical site infections as an endpoint. Data on surgical site infections are collected according to international standards defined by the Centers for Disease Control and Prevention (CDC) by the surveillance system of Swissnoso—the national center for the prevention of infections in Switzerland. Type 1 (superficial), type 2 (fascial), and type 3 (organ/space) infections are distinguished (91). Swissnoso collects data only in Switzerland and only for a subset of operations. The data will be obtained from Swissnoso and form a pragmatic subsample of data that is available.

### Withdrawal and discontinuation

Based on the previous study (StOP? I) [31], retention problems with regard to surgeons and patients are likely to be very low. This assumption is justified by the relatively short enrollment period per surgeon and the short follow-up for the primary endpoint. Even if patients drop out, ascertaining whether patients are alive at 30 days is often still possible. With regard to patient retention, the biggest risk is that patients do not give or withdraw consent to use their data which we deem unlikely given the low patient burden.

### Randomization

#### Allocation sequence

Enrolled clusters will be randomized in a 1:1 fashion to either the StOP? or the standard arm. Randomization will be stratified by surgical department and seniority (Chef-/Leitende Ärztin/Arzt versus other).

#### Concealment mechanism

Allocation will be done using a web-based system, which also contains the electronic case report form (eCRF): REDCap. The system reveals the allocation only after a cluster is definitely enrolled in the trial, i.e., eligibility criteria confirmed.

#### Implementation

Dedicated study personnel will establish a list of eligible surgeons. After obtaining informed consent from the surgeons, the responsible study personnel will transfer the list of enrolled clusters to CTU Bern. There, an independent data manager will allocate these clusters to the two trial groups (batch randomization) and will create a new cluster record within the web-based system. The system will disclose the assignment only after the completion of this registration.

### Statistical analysis plan and sample size calculation

#### Sample size calculation

Sample size calculations were based on the primary objective, i.e., whether patients in the StOP? intervention group have a lower risk of mortality compared to patients in the standard of care group. The primary effect measure will be odds ratio as the primary analysis will be based on a logistic regression (see below). Based on the data from the first StOP? study, we calculated an intracluster correlation coefficient (ICC) of 0.024 from a mixed-effects logistic model. Also, we estimated 30-day mortality from the before phase of the StOP? study and use this number (1.8%) for the event rate in the control group. The target treatment effect that we do not want to miss is an odds ratio of 0.5, i.e., we aim to reduce mortality in the StOP? intervention group to 0.9%. Sample size calculations were done in Stata (release 16.1) using the power twoproportions command with the cluster option. The command calculates power based on a *z*-test with standard error adjusted by the intracluster correlation and varying cluster size. With 400 clusters overall (with 1:1 allocation, i.e., 2 × 200), an average size of 24 patients per cluster, and a coefficient of variation of 0.5, we will achieve 84% power at a significance level of 0.05 (two-sided).

We assume that some patients will be operated by two disparate surgeons (i.e., two surgeons randomized to different trial arms are performing one operation jointly). To accommodate this, we fixed the target average cluster size at 30 patients. This sample size allows for varying cluster sizes to accommodate differences in operation volume across clusters (coefficient of variation of 0.5, i.e., cluster size is allowed to range between 10 and 50 patients). A minimum of 12,000 patients will be required. Based on the experience of the StOP? I study, we expect that some surgeons perform many more operations than the assumed upper cluster size. Therefore, we expect that 14,000 patients will be enrolled overall. Given the relatively low number of events, we performed simulation studies to check the robustness of the assumption of an asymptotically normally distributed test statistic. Using a random-effects logistic regression in 1000 simulated trials with the same assumptions as described above, we calculated a power of more than 90%.

We also performed several sensitivity analyses to account for the uncertainty of our assumptions, e.g., (1) allowing for a larger variation in cluster size (coefficient of variation of 0.7) results in 82% power; (2) allowing for the unlikely case of higher intracluster correlation (ICC of 0.03) results in 80% power; and (3) allowing for enrolment problems i.e., 370 clusters but similar cluster size results in 80.9% power or a similar number of clusters but smaller average cluster size (21 patients) results in 80.6% power.

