#### Interim analyses

We will conduct one interim analysis after endpoint data were completely collected for 200 clusters. We will reassess the ICC based on the data collected to adjust the sample size if needed. To calculate the ICC, we will use multilevel mixed-effects logistic regression. If the ICC is > 0.024, we will perform new power calculations using the same assumptions as in the original sample size calculation. Based on these calculations, we will increase the number of clusters and/or the number of patients per cluster except if the required increase would be too large to be feasible. Because the type I error is not affected by the recalculation of the ICC, we will not adjust the significance level.

Moreover, an interim analysis of the primary outcome will be performed to examine the trial for potential futility: The conditional power for a statistically significant difference between the intervention and control groups at the end of the study will be estimated based on data collected at the time of the interim analysis. If the conditional power is < 20%, it is recommended to terminate the trial for futility. Implications for type I and II errors are minimal, so no adjustment is needed for this type of interim analysis [45].

Given that no interim analysis for safety or efficacy will be done, no independent Data Monitoring Board (iDMC) is established, and possible sample size adaptations or trial termination for futility will be decided by the Steering Committee.

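### Two mortality figures, about 1% and 1.8%, stand unreconciled; the 84% power depends on the higher one, and the interim recalculation keeps it fixed

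*Protocol article*

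**What the plan says.** All references are to the protocol article.

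- **Sample size calculation, control rate.** The source is the authors' previous study: "we estimated 30-day mortality from the before phase of the StOP? study". The authors "use this number (1.8%) for the event rate in the control group".
- **Sample size calculation, effect and size.** The target is "an odds ratio of 0.5, i.e., we aim to reduce mortality in the StOP? intervention group to 0.9" percent. The size is given as "With 400 clusters overall (with 1:1 allocation, i.e., 2 × 200), an average size of 24 patients per cluster". With an ICC of 0.024 and a cluster-size coefficient of variation (CV) of 0.5, the authors state that "we will achieve 84% power at a significance level of 0.05 (two-sided"). A simulation with random-effects logistic regression under the same assumptions gave more than 90%.
- **Sample size calculation, sensitivity analyses.** The listed scenarios change the CV, the ICC, the number of clusters and the mean cluster size.
- **Study sites.** The choice of specialties was "guided by the mortality rates of about 1% in these specialties", and this level is described as comparable to the general and abdominal surgery of StOP? I.
- **Interim analyses.** After 200 clusters the ICC is reassessed. "If the ICC is > 0.024, we will perform new power calculations using the same assumptions as in the original sample size calculation". A separate futility look may stop the trial if conditional power is below 20%.

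**The concern.** The same earlier study is described as comparable to about 1% in one section and supplies 1.8% in another. According to the Abstract, StOP? I was performed mainly in visceral surgery, and the present trial deliberately covers a wider range of specialties. The article does not explain why 1.8% carries over to that wider case mix.

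With a rare binary endpoint, information comes mainly from the number of deaths, so the control rate is a leading driver of power. If the true rate is nearer 1%, the trial has fewer events than planned. The step meant to correct planning assumptions would then leave this one untouched: it reacts only to a high ICC, and even then the 1.8% is used again. The futility rule can end an underpowered trial but cannot enlarge it.

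**Working it through.** **Inputs** (all from Sample size calculation unless noted): control rate pc = 1.8%; odds ratio 0.5; 200 clusters per arm; mean size m = 24; CV = 0.5; ICC ρ = 0.024; two-sided α = 0.05; z-test for two proportions with a cluster-adjusted standard error. Alternative control rate: about 1% (Study sites).

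**Step 1: reproduce the stated power.**

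Design effect for unequal clusters: DE = [1 + (m − 1)ρ] / [1 − CV²·λ(1 − λ)], with λ = mρ / (mρ + 1 − ρ).

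- λ = 0.576 / 1.552 = 0.371
- DE = 1.552 / (1 − 0.25 × 0.371 × 0.629) = 1.552 / 0.942 = 1.648
- Effective n per arm = 4,800 / 1.648 = 2,912
- Odds ratio 0.5 from 1.8% gives 0.908%, a difference of 0.892 percentage points
- Power = Φ[(0.00892 − 1.96 × 0.00303) / 0.00303] = Φ(0.985) = 83.8%. Stated: 84%.

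The same formula gives the listed sensitivity figures:

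| Scenario | Recomputed | Stated |
|---|---|---|
| CV 0.7 | 81.5% | 82% |
| ICC 0.03 | 80.5% | 80% |
| 370 clusters | 80.9% | 80.9% |
| 21 per cluster | 80.6% | 80.6% |

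All agree to within about half a point, so this is very probably the calculation that was run.

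**Step 2: change only the control rate.** At 1.0%, odds ratio 0.5 gives 0.5025%. Power = Φ[(0.00497 − 1.96 × 0.00226) / 0.00226] = Φ(0.239) = 59.4%.

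| Control rate | z-test, 24 per cluster | z-test, 30 per cluster |
|---|---|---|
| 1.8% | 84% | 88% |
| 1.4% | 74% | 79% |
| 1.2% | 67% | 73% |
| 1.0% | 59% | 65% |

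The more common design effect 1 + ρ[(1 + CV²)m − 1] = 1.696 gives nearly the same result: 83% at 1.8% and 58% at 1.0%. The four listed scenarios cost roughly 2 to 4 points each; the move to 1.0% costs about 25.

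Expected deaths in 400 × 24 = 9,600 patients: 4,800 × (0.018 + 0.009) = 130, against 4,800 × (0.010 + 0.005) = 72.

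**Step 3: allow for the ICC scale.** The ICC came from a mixed-effects logistic model. Assume it is on the latent logistic scale. The between-surgeon variance is then 0.024 / 0.976 × π²/3 = 0.081. The approximate ICC on the proportion scale is p̄(1 − p̄) × 0.081, with p̄ the mean of the two arm rates: 0.0011 at 1.8% and 0.0006 at 1.0%. The design effect at m = 24 drops to about 1.03 and 1.02.

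| Control rate | 24 per cluster | 30 per cluster |
|---|---|---|
| 1.8% | 96% | 99% |
| 1.4% | 91% | 96% |
| 1.2% | 86% | 93% |
| 1.0% | 80% | 88% |

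A simulation of clustered data on this assumption, tested with a cluster-robust z-test on the log odds ratio, gave 97% at 1.8% and 81% at 1.0% with 24 per cluster, and 89% at 1.0% with 30.

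**Step 4: check the safeguards.** None of the listed sensitivity scenarios changes the event rate. The interim recalculation is triggered by the ICC alone and otherwise keeps the original inputs. Futility uses interim data but leads only to stopping or continuing.

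**The case against.** The strongest defence has four parts.

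1. **The 1.8% has a named empirical source.** It comes from the before phase of a study of 8,256 operations. The 1% is a rounded literature figure used to select specialties. Eligibility is also narrower than a specialty: emergencies are in, while outpatient-clinic procedures, mainly diagnostic endoscopy and percutaneous interventions are out. The rate among eligible operations could exceed the specialty average. This stands. A reader might infer that 1% is the right control rate, or that the two figures cannot both be true of their own populations; the document supports neither. It leaves the gap unexplained, although it calls the 1% comparable to the very study that yielded 1.8%.

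2. **The z-test may be conservative.** If the ICC is a latent-scale value, power at 1.0% is about 80% with 24 per cluster and about 88% at the target size of 30. The plan's simulation above 90% fits this reading and is closer to the planned mixed model. This stands as an assumption and removes much of the loss. However, 24 rather than 30 is the plan's own allowance for operations shared between arms, so the 88% ignores that dilution. The stated 84% and its sensitivity figures also rest on the z-test.

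3. **The sensitivity list is introduced as examples.** An event-rate scenario may exist in the full protocol. This is fair, so the point is limited to what is listed.

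4. **Pooled endpoint counts are reported yearly** under (Periodic) safety reporting, so a low rate would be noticed. That is true, but no rule links those counts to the sample size.

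**Conclusion.** The point holds as an unsupported planning assumption combined with a badly fixed interim rule. It should be fixed, but it does not invalidate the design.

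A reader might infer that the 84% is miscalculated. It is not; it follows from its inputs. A reader might also infer that the trial has only 59% power. That needs both a control rate of 1.0% and an ICC of 0.024 applied directly to proportions, and the document establishes neither.

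What can be said is this. With 24 per cluster and odds ratio 0.5, going from 1.8% to 1.0% lowers power from about 84% to 59% by the plan's z-test, or from about 96% to 80% if the ICC is on the latent scale. Under both readings, power depends materially on a rate for which the document gives two values, and the planned recalculation cannot correct it.

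**What to change.** 1. **Reconcile Study sites with Sample size calculation.** Explain why 1.8% is expected among eligible operations in the wider set of specialties, or revise it.
2. **Report power across control rates of 1.0% to 1.8%** in Sample size calculation and among its sensitivity analyses, and say whether the ICC of 0.024 is on the latent or the proportion scale.
3. **Change the Interim analyses rule.** At the existing look, re-estimate 30-day mortality pooled over arms together with the ICC. Recompute power with both at odds ratio 0.5, whether or not the ICC exceeds 0.024, and let that result drive any increase within the feasibility limit already stated. Under odds ratio 0.5, a pooled rate of about 1.35% corresponds to 1.8% in controls and about 0.75% to 1.0%. With 200 clusters of 24 (4,800 patients) that is about 65 against 36 deaths, so the look is informative.

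**Cost:** some protocol wording and one more step in the interim program. The pooled rate does not reveal the treatment difference, so no alpha adjustment is needed. The stated power will look less favourable. If the rate proves near 1.0%, the z-test would ask for about 650 clusters of 24 for 80% power, which may exceed what is feasible; on the latent-scale reading, 400 clusters already give about 80%. That is why the ICC scale should be settled before the interim look.
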